### Randomisation

Randomisation of the study sample in intervention group and control group takes place on the school level and is done before pre-test data assessment by a researcher of the study team (see Fig. 3). A computer-based random number producing algorithm is generated and completed by an independent researcher to ensure an equal chance of allocation of a school to either group. No matching is undertaken. Factors differentiating between classes or schools are compensated by use of a multilevel analysis (see statistical analysis).

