Main part	• *Intervention programme*	On the basis of a detailed discussion of the lesson plans, the teacher should develop a feeling for how to teach the PE lessons so that the constructs can be promoted. Remarks and challenges that may arise during the implementation of the lessons are addressed and discussed. The main part ends with a discussion of the study organisation, especially the offering of continuous mentoring throughout the intervention period.
	o Structure of the project portfolio	
	o (series of teaching lessons, additional materials)	
	o Series of lesson plans	
	­ Structure and overview	
	- Teaching units and curriculum	
	- Focus on single lesson plans and the applied behaviour change techniques	
	- General remarks and possible challenges	
	• *Study organisation*	
	o Timeline	
	o Methods of data collection	
	o Mentoring (phone, e-mail)	
End	• *Discussion and closing-remarks*	Questions are clarified, further suggestions are made and a conclusion is carried out.

In *pilot study 3*, each of the six trained teachers carried out five PE lessons of one teaching unit (fitness & health, dance, gymnastics, basketball, soccer) and provided information on a) the feasibility of the lessons according to different criteria (content, goals, time, etc.) using a checklist provided by the researchers and b) the overall lesson plans based on notes the teachers took during the lesson. Additionally, using a modified version of the System for Observing Fitness Instruction Time (SOFIT), the extent to which the central constructs of the intervention programme were promoted within the PE lessons was captured. Therefore, the measuring instrument was adapted in such a way that the original three observation categories “physical activity”, “lesson content/context” and “teacher behaviour” were replaced by the promotion of the three constructs “autonomy”, “competence” and “relatedness”. In addition, the observation interval was extended from ten to 30 s. This systematic observation was carried out in two of the five PE lessons held by each teacher.

In order to recruit a study sample of 600 girls several study waves will be necessary. The first study wave was conducted in the school year 2017/2018 and a second study wave 2018/2019 is currently under way.

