### Statistical analysis

Structural equation modeling in R will be used to examine the scientific questions outlined above. To evaluate the effect of the intervention, a multiple group analysis with the intervention and control group will be performed. To account for the clustered nature of the study sample, physical activity will be included in four levels. Level 1 will be the repeated measurements for each individual, level 2 will be the individual itself in which the repeated measurements are nested. Level 3 stands for the class the individual is part of. The class is again nested within a certain school, which represents level 4. The basis for this approach is the assumption, that physical activity is not only influenced by the individual’s personal attitudes and preferences but also by the attitudes and behaviour of the class teacher as well as by the school environment. In a further step, the model will be explicitly extended by the potential moderators BMI, socioeconomic status as well as characteristics of teacher and environment to check if they exert a significant influence on the effect of the intervention.

To gain a deeper insight into the mechanisms of physical activity behaviour change, the girls’ physical activity will be regressed onto the potential mediators. This way, it can be examined which mediators are of incremental importance in relation to the other mediators included in the model concerning the promotion of physical activity. Thereby, the assumed mediators will each be included in three levels.

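### The Randomisation section says the multilevel analysis compensates for class and school differences, but the nesting levels described account for clustering and do not adjust the arm contrast for uneven school factors

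*Protocol article*

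**What the plan says.** Under Randomisation, the protocol article says that allocation "takes place on the school level and is done before pre-test data assessment by a researcher of the study team". It uses computer-generated random numbers "to ensure an equal chance of allocation of a school to either group". It then states "No matching is undertaken", followed directly by the claim that "Factors differentiating between classes or schools are compensated by use of a multilevel analysis", with a pointer to the statistical analysis.

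Under Statistical analysis, the effect is to be evaluated thus: "a multiple group analysis with the intervention and control group will be performed". The multilevel part is introduced with "To account for the clustered nature of the study sample, physical activity will be included in four levels": repeated measurements, girl, class and school. Covariates appear only afterwards: "In a further step, the model will be explicitly extended by the potential moderators BMI, socioeconomic status as well as characteristics of teacher and environment". The stated purpose of that step is to see whether they influence the intervention effect.

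Under Procedure: "In order to recruit a study sample of 600 girls several study waves will be necessary". The first wave ran in school year 2017/2018, and the second (2018/2019) was under way.

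**The concern.** The sentence gives the multilevel model a property it does not have. Random effects for school and class describe how outcomes correlate within clusters, and so make the standard error honest. Every girl in a school is in the same arm. In a comparison of outcome levels, a school term therefore cannot separate the arm from whatever else distinguishes the schools in that arm. Adjustment needs either a balancing device at allocation or fixed covariates in the main-effect model. The only named covariates enter later, as moderators.

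The article itself assumes that activity depends on the class teacher and the school environment, so by its own reasoning these factors matter. If readers and analysts believe imbalance is already dealt with, a chance difference between arms will be left in the estimate, and precision that T1 activity, wave and socioeconomic status could recover may be lost.

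**Working it through.** **1. The plan's own figure.** The only computed design figure is the sample size (467, raised to 600). It does not bear on this point, and the article does not give the SD and mean cluster size needed to reproduce it.

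**2. Does nesting remove a school-level shift?** All inputs here are assumed: 20 schools (10 per arm), 2 classes per school, about 15 girls per class, cluster-size CV 0.25 (the article's value), SD 30 min/day and true effect 0. Variance shares at one time point are school 0.08, class 0.05 and remainder 0.87. A school factor worth 10 min/day is present in 7/10 intervention and 3/10 control schools.

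Expected shift = 10 × (0.7 − 0.3) = 4.0 min. Means over 300 simulated trials, factor constant over time:

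| Analysis | Estimate | SE |
|---|---|---|
| T2 level, no random effects | 3.75 | 2.47 |
| T2 level, school and class random effects | 3.82 | 4.93 |
| As above, plus the factor as fixed covariate | −0.23 | 5.38 |

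Check of the second SE: variance of a school mean = 900 × (0.08 + 0.05/2 + 0.87/30) = 72 + 22.5 + 26.1 = 120.6, and √(2 × 120.6/10) = 4.91. The Monte Carlo error of the mean estimate is about 4.93/√300 = 0.28, so 3.75 and 3.82 both agree with 4.0. The random effects doubled the SE and left the shift where it was.

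The simulation held the variance components at their values without the factor. If estimated, the school variance would absorb the factor: 72 + 100 × 0.7 × 0.3 = 93, which gives SE = √(2 × 141.6/10) = 5.32. That is how the model covers imbalance on average: through a wider interval, not a corrected estimate.

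**3. Does the T1 measurement rescue the claim?** Same scenario, change from T1 to T2, with school and class structure:

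| Factor | Change contrast | Change contrast plus covariate |
|---|---|---|
| Constant over time | −0.05 | −0.01 |
| Acts on change only | 4.08 | −0.13 |

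A stable school difference cancels, because the baseline is subtracted and not because of the nesting. A factor that acts on change (teacher, environment and study wave are candidates) stays in full.

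**4. How often would a school factor be uneven?** Assume a factor present in half of the schools and an independent equal-chance allocation. The probability that its prevalence differs by at least 30 percentage points between arms is:

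| Schools | 10 | 14 | 20 | 30 | 40 |
|---|---|---|---|---|---|
| Probability | 36% | 25% | 27% | 11% | 8% |

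With 20 schools forced to 10:10 it is 18%.

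**5. Uneven numbers of schools.** Variance factor = (1/a + 1/b) ÷ (4/K) for a split a:b of K schools.
- One wave of 8: 6:2 gives 0.667/0.5 = 1.33, and the probability of 6:2 or worse is 74/256 = 29%. One wave of 10: 7:3 gives 0.476/0.4 = 1.19, probability 352/1024 = 34%.
- Two such waves pooled, same penalties: 12:4 or worse of 16 has probability 2 × 2517/65536 = 7.7%, and 14:6 or worse of 20 has 2 × 60460/1048576 = 11.5%.

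If waves are pooled, the second line is the relevant one.

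**6. Precision from baseline adjustment.** At individual level, the ratio of variances (baseline-adjusted to change score) = (1 − r²)/[2(1 − r)] = (1 + r)/2. For assumed r = 0.3, 0.5 and 0.7 this is 0.65, 0.75 and 0.85, a saving of 35%, 25% and 15%. In a school-randomised trial the saving also depends on how school and class means correlate over time, so these figures show direction and rough scale only.

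**The case against.** The best defence is that the planned model contains T1 as a level-1 measurement. All schools are untreated at T1, so an effect defined as difference in change is not confounded with stable school differences, and for those the plan achieves in practice what it claims. This stands for time-constant factors, as step 3 shows. It does not save the sentence: the article does not say how T1 enters the two-group model, the cancellation comes from the baseline measurement, and factors acting on change are untouched. Regression to the mean after a chance baseline difference also remains.

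A second defence is that a condensed article may leave covariates to an analysis plan. That is fair, and the missing list of covariates is not the point. The point is a positive statement about what the described analysis does.

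Some stronger readings are tempting but unsupported:
- That allocation is simple randomisation, chosen because of the multilevel claim. The text gives only equal chance and no matching, which do not exclude blocking, and it states no causal link.
- That there are few schools. No number is given.
- That T1 means are free in each arm. No constraint is stated either way.
- That baseline imbalance simply stays in the estimate. In a change contrast it is subtracted.
- That there is a 29% to 34% chance of a costly split. Those figures describe one assumed wave.

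**Conclusion.** The statement is wrong as written and should be corrected. The described nesting accounts for clustering and does not compensate for school factors that differ between arms. The trial's validity is not at stake: even unrestricted randomisation of schools is unbiased in expectation, and a standard error that includes school variance covers chance imbalance on average. What remains is distortion in the particular allocation obtained, and avoidable loss of precision.

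The size cannot be stated for this trial, because the number of schools and the T1-T2 correlation are not given. Under the assumed scenario, a 10 min/day factor split 7:3 against 3:7 moves the estimate by about 4 min/day, against a planned effect of 20 min/day. It does so in a comparison of T2 levels, or in a change contrast if the factor acts on change.

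**What to change.** 1. **Reword the Randomisation sentence** to say that the multilevel model accounts for clustering within classes and schools, and that it does not correct for imbalance between arms.
2. **Adjust the main-effect model for baseline activity in one stated way:** either T1 as a covariate with T2 and T3 as outcomes, or T1 as an outcome with a common baseline mean across arms. Doing both would use T1 twice.
3. **Add study wave and socioeconomic status as fixed covariates** in that model, separately from the later moderator step.
4. **Optionally, block the allocation within wave** for any schools not yet allocated. Do not constrain it on socioeconomic status measured at T1, since that comes after randomisation.

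T1 activity and socioeconomic status are already collected and wave is known, so items 1 to 3 cost a few model parameters and also serve waves already randomised. T1 values are taken before the intervention but after allocation, so the adjustment assumes that allocation did not affect who took part or what was recorded at T1. Item 4 needs a new allocation list, and how many schools it could still reach is not known from the article.

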### Procedure

Before the beginning of the main intervention study, *three pilot studies* were carried out to examine 1) the measurement applicability and the quality criteria of the instruments, 2) the feasibility of the teacher training programme and 3) the feasibility of the intervention programme (see Fig. 3).

In *pilot study 1*, 161 sixth grade students filled out questionnaires and wore accelerometers measuring their physical activity for six days. The instruments (see Additional file 1: Table S1) used to assess the constructs of need satisfaction in PE and leisure time, intrinsic motivation, self-efficacy and social support of family and friends had been translated and adjusted to the stage of development regarding language of sixth-graders before. The adapted scales have shown acceptable to good quality criteria.

In *pilot study 2*, six teachers were trained individually by one researcher in one session with two hours at school or university location. The training was carried out with a prepared project portfolio, presentations, interaction forms and visual materials (see Table 1). Following the training, a guided interview was conducted by a second researcher to obtain information about the success of the training regarding a) teaching and mediation competence of the trainer, used methods and materials, consideration and satisfaction of the teachers’ needs and expectations, b) whether the teachers felt in a position to implement the intervention as planned, areas in which they did not feel sufficiently competent or anticipate possible challenges or difficulties and c) to receive teachers’ comments on improvements in the teacher training and general remarks.

**Table 1 Tab1:** Teacher training programme

	Content	Detailed description
Introduction	• *Welcome and programme overview*	In the introductory section, a general overview of the project is given after the welcome part. Subsequently, the underlying theories and current state of research are comprehensively addressed. The focus will be on an understanding of the promoted constructs within the intervention programme and of the corresponding behaviour change techniques.
	• *Project introduction*	
	• *Theoretical background*	
	o Current state of research: theories (YPAPM, self-determination theory, social cognitive theory)	
	o Constructs: autonomy, competence, relatedness, self-efficacy, social support	
	o Behaviour Change Techniques	
Main part	• *Intervention programme*	On the basis of a detailed discussion of the lesson plans, the teacher should develop a feeling for how to teach the PE lessons so that the constructs can be promoted. Remarks and challenges that may arise during the implementation of the lessons are addressed and discussed. The main part ends with a discussion of the study organisation, especially the offering of continuous mentoring throughout the intervention period.
	o Structure of the project portfolio	
	o (series of teaching lessons, additional materials)	
	o Series of lesson plans	
	­ Structure and overview	
	- Teaching units and curriculum	
	- Focus on single lesson plans and the applied behaviour change techniques	
	- General remarks and possible challenges	
	• *Study organisation*	
	o Timeline	
	o Methods of data collection	
	o Mentoring (phone, e-mail)	
End	• *Discussion and closing-remarks*	Questions are clarified, further suggestions are made and a conclusion is carried out.

In *pilot study 3*, each of the six trained teachers carried out five PE lessons of one teaching unit (fitness & health, dance, gymnastics, basketball, soccer) and provided information on a) the feasibility of the lessons according to different criteria (content, goals, time, etc.) using a checklist provided by the researchers and b) the overall lesson plans based on notes the teachers took during the lesson. Additionally, using a modified version of the System for Observing Fitness Instruction Time (SOFIT), the extent to which the central constructs of the intervention programme were promoted within the PE lessons was captured. Therefore, the measuring instrument was adapted in such a way that the original three observation categories “physical activity”, “lesson content/context” and “teacher behaviour” were replaced by the promotion of the three constructs “autonomy”, “competence” and “relatedness”. In addition, the observation interval was extended from ten to 30 s. This systematic observation was carried out in two of the five PE lessons held by each teacher.

In order to recruit a study sample of 600 girls several study waves will be necessary. The first study wave was conducted in the school year 2017/2018 and a second study wave 2018/2019 is currently under way.

### Intervention programme

The intervention programme is delivered by the PE or regular class teachers during PE classes. The teachers carrying out the intervention programme are provided with all the materials required for the implementation of the intervention programme during the teacher training session before the programme begins.

The materials include examples of how different behaviour change techniques can be applied to address the girls’ *autonomy*, *competence* and *relatedness* during PE. Most importantly, they receive fully elaborated lesson plans. These lessons combine the requirements of the PE curriculum and the behaviour change techniques by Michie, Richardson [12] in order to establish a change in the targeted mediating variables (see Table 2). The teachers will be asked to implement the lesson plans as thoroughly as possible during the five-month intervention period. Due to the extensive conceptual similarities of self-efficacy and competence as well as relatedness and social support, it is refrained from presenting special behaviour change techniques for the constructs of self-efficacy and social support.

**Table 2 Tab2:** Theory-based mediators and corresponding behaviour change techniques

YPAPM	Theory	Mediator	Behaviour change techniques (13)
Predisposing Individual level	Self-determination theory	Competence	(2.2) Feedback on behaviour: The teacher provides feedback on performance of the physical activity behaviour during PE and informs the students whether they were active during the lesson and how they can improve their activity levels. (8.7) Graded tasks: The teacher sets easy-to-perform tasks in and after PE, making them increasingly difficult, but achievable, until behaviour is performed. (8.1) Behavioural practice/rehearsal: Sufficient practice time should be included in each PE lesson. Moreover, practice or rehearsal of the performance of the behaviour should be prompted once or more times in a context or at a time when the performance may not be necessary, in order to increase habit and skill without any social pressure.
	Self-determination theory	Autonomy	Providing choice [38]: The teacher supports students’ autonomy during PE by providing them a choice between different contents during the PE lesson and for different activities during the afternoon.
Reinforcing Interpersonal	Self-determination theory	Relatedness	(3.1) Social support: Teachers advise on, arrange or provide social support (e.g. from friends and parents) or non-contingent praise or reward for performance of the behaviour.

### Measures

All measures used in this study can be found in the Additional file 1: Table S1.

### Statistical analysis

Structural equation modeling in R will be used to examine the scientific questions outlined above. To evaluate the effect of the intervention, a multiple group analysis with the intervention and control group will be performed. To account for the clustered nature of the study sample, physical activity will be included in four levels. Level 1 will be the repeated measurements for each individual, level 2 will be the individual itself in which the repeated measurements are nested. Level 3 stands for the class the individual is part of. The class is again nested within a certain school, which represents level 4. The basis for this approach is the assumption, that physical activity is not only influenced by the individual’s personal attitudes and preferences but also by the attitudes and behaviour of the class teacher as well as by the school environment. In a further step, the model will be explicitly extended by the potential moderators BMI, socioeconomic status as well as characteristics of teacher and environment to check if they exert a significant influence on the effect of the intervention.

To gain a deeper insight into the mechanisms of physical activity behaviour change, the girls’ physical activity will be regressed onto the potential mediators. This way, it can be examined which mediators are of incremental importance in relation to the other mediators included in the model concerning the promotion of physical activity. Thereby, the assumed mediators will each be included in three levels.

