### Sample size calculation

The sample size needed to detect the intended increase in physical activity from baseline to post-intervention was calculated using the formula by Rutterford, Copas [32], who consider several aspects of cluster randomisation, e.g., the intended effect of the intervention, the estimated intracluster correlation (ICC), potentially variable cluster sizes and the implied levels of significance and power. To include appropriate figures for the respective parameters, it is referred to previous research. An intervention-based increase of twenty minutes per day of moderate-to-vigorous physical activity is estimated based on the systematic review by Camacho-Minano, LaVoi [33]. An ICC at the class-level of 0.1 appears appropriate based on the study by Lonsdale, Rosenkranz [34]. Additionally, to account for variable cluster sizes (i.e. number of students within the respective classes) in the present study, we estimate a variation coefficient of the cluster size of 0.25. By inserting the specified figures for the respective parameters and setting an alpha of 0.05 and a power level of 80%, a sample size of at least 467 is required to detect the intended baseline-intervention change in physical activity. Finally, taking dropouts into consideration a sample size of 600 is sought.

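### H1 is assigned to a multiple-group SEM whose default inference is large-sample in the randomised schools; with few schools and no correction, its nominal 5% test could reject at about 5-14%

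*Protocol article*

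**What the plan says.** Under Statistical analysis, the protocol article states: "Structural equation modeling in R will be used to examine the scientific questions outlined above". For the intervention effect it adds: "To evaluate the effect of the intervention, a multiple group analysis with the intervention and control group will be performed". Physical activity enters at four levels: measurement, girl, class and school. Moderators are added to this model in a later step.

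Under Randomisation: "Randomisation of the study sample in intervention group and control group takes place on the school level". There is no matching, and the section relies on the multilevel analysis to deal with differences between classes and schools.

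The significance level appears only under Sample size calculation ("setting an alpha of 0.05 and a power level of 80" per cent). The clustering inputs there concern classes: "An ICC at the class-level of 0.1 appears appropriate", and "we estimate a variation coefficient of the cluster size of 0.25".

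The article does not give the number of schools, the classes per school, the mean class size, a school-level ICC, the estimator, the type of test or its reference distribution. It also does not say whether variances are held equal across arms.

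**The concern.** Every girl in a school is in the same arm. When schools differ from one another, the precision of the arm contrast is limited by the number of schools, not by the 600 girls.

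Two features of default SEM inference then work in the same direction. Maximum likelihood understates the school-level variance, by a factor of about (k-1)/k with k schools per arm. The normal or chi-square reference treats that estimate as known, although it carries only about 2(k-1) degrees of freedom.

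The result can be a standard error that is too small and a critical value that is too low. H1 would be declared significant more often than the planned 5%, and its confidence interval would be too narrow. The level assumed in the sample size would not be the level of the analysis.

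**Working it through.** **The plan's own figure.** The article reports that "a sample size of at least 467 is required to detect the intended baseline-intervention change in physical activity". The stated inputs are a 20 min/day effect, class ICC 0.1, cluster-size CV 0.25, alpha 0.05 (taken as two-sided) and power 80%. The total is 4 x (1.96 + 0.842)^2 x SD^2 / 20^2 x [1 + ((1 + 0.25^2) x m - 1) x 0.1], where m is the mean class size. The SD and m are not given, so 467 can be neither confirmed nor refuted. It results from m = 15 with SD 48.8, m = 20 with SD 44.3, or m = 25 with SD 40.9. It does not fix the number of schools.

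**Number of schools (assumption).** With 25 girls per class and 3 classes per school, 600/75 = 8 schools. With 12 girls and 1 class per school, 600/12 = 50.

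**Closed form.** This takes balanced arms, k schools per arm, and all error in the contrast at school level. For the ML Wald test with a z cut-off, type I error = P(|t with 2(k-1) df| > 1.96 x sqrt((k-1)/k)). For 8 schools, k = 4, the cut-off is 1.96 x sqrt(3/4) = 1.697 on 6 df, which gives 14.1%.

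| Schools | ML Wald | z cut-off alone | Likelihood ratio |
|---|---|---|---|
| 8 | 14.1% | 9.8% | 10.3% |
| 12 | 10.4% | 7.8% | 8.1% |
| 20 | 7.9% | 6.6% | 6.7% |
| 30 | 6.9% | 6.0% | 6.1% |
| 50 | 6.1% | 5.6% | 5.6% |

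In the balanced case these figures are the same whether the school variance is pooled or estimated by arm.

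**Simulation.** The closed form is a worst case, because some clustering may lie at class level. The simulation used 200,000 null trials per setting, about 600 girls, one change score per girl, total ICC 0.1, and ML with variances held non-negative. Entries are the Wald test with arm-specific variances / the likelihood-ratio test with pooled variances.

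| Schools x classes x girls | School ICC 0 | 0.02 | 0.05 | 0.10 |
|---|---|---|---|---|
| 8 x 3 x 25 | 6.1 / 5.0% | 8.7 / 7.2% | 11.7 / 9.3% | 13.7 / 10.2% |
| 12 x 2 x 25 | 6.1 / 5.3% | 7.4 / 6.4% | 9.0 / 7.5% | 10.3 / 8.1% |
| 20 x 2 x 15 | 5.4 / 5.0% | 6.3 / 5.7% | 7.2 / 6.4% | 7.9 / 6.7% |
| 50 x 1 x 12 | - | - | - | 6.0 / 5.6% |

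Pooling the variances across arms changes the Wald figures little (13.9% instead of 13.7% in the top right cell).

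**After correction.** A t reference with schools minus 2 df and an unbiased school variance gives 5% by construction in the balanced case. In a separate simulation of 8,000 null trials per setting, a t test on school means gave 4.7-5.2%.

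**Cost in width.** The interval widens by (t critical / 1.96) x sqrt(k/(k-1)). With 12 schools this is (2.228/1.96) x sqrt(6/5) = 1.245. With 20 schools it is 1.13, and with 50 it is 1.05.

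**The case against.** The strongest reply has four parts.

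- **School is already in the model.** This stands. The plan respects the unit of randomisation, and what remains is a small-sample question.
- **The article names a model family, not a test.** It fixes no Wald test, no z reference and no arm-specific variances, and a condensed article may leave such details to a fuller document. This stands in part. The absence of a degrees-of-freedom rule is not an error in itself. But the article does commit H1 to a multiple-group SEM, whose usual inference is large-sample, whereas the standard small-sample corrections belong to linear mixed models.
- **The inflation depends on unstated inputs.** This stands. With 50 schools it is about one percentage point. With no school-level variance, the likelihood-ratio test stays near 5% even with 8 schools. The only ICC in the article is at class level.
- **Replacing the model by an analysis of T2 alone would discard the planned repeated measures.** This is a fair limit on the remedy. The replacement can keep T1, T2 and T3.

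**Conclusion.** The concern holds in conditional form. If H1 is tested by the default large-sample Wald inference of the named model, its type I error at nominal 5% is about 5-14% over 8 to 50 schools: about 6-14% with 8, 5-8% with 20 and 6% with 50. The upper end needs few schools and clustering mainly at school level.

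The range rests on the assumed 12-25 girls per class and 1-3 classes per school, a total ICC of 0.1 and balanced arms. Ten girls in one class per school would allow 60 schools, with a Wald error of about 5.9%.

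Two stronger readings are tempting, and the article supports neither. A reader might infer that the analysis ignores the randomised unit, but school is its fourth level. A reader might also infer that the H1 test is known to reject at well above 5%, but the number of schools, the school-level share of the clustering and the type of test are all unstated. What can be said is that the named method gives no protection if the schools are few, and that a standard alternative does.

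**What to change.** Test H1 in one linear mixed model for physical activity, with arm as a fixed effect and random effects for school and class. Either keep the T1/T2/T3 repeated measures and test arm-by-time (with a girl-level random effect), or model T2 adjusted for T1. Fit by REML with Kenward-Roger or Satterthwaite degrees of freedom, or use a t reference with about the number of schools minus 2 df. Test the moderators as arm-by-moderator terms in the same model. Keep the SEM for H2a-H2e. State the number of schools, so that a reader can judge how much the correction matters.

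This takes about one paragraph of analysis wording and no new data. The price is a wider interval for the arm effect: about 25% with 12 schools, 13% with 20 and 5% with 50, if clustering is mainly at school level.
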